### 2.2. Participants

The sample size was estimated using G*Power (version 3.1., University of Düsseldorf, City, Germany) [28]. A priori power analysis, based on the Wilcoxon signed-rank test, was conducted with an alpha level of 0.05, statistical power of 0.80, and a moderate effect size (Cohen’s d = 0.5). The analysis determined that 67 participants were required. To account for potential dropouts, the final sample size was set at 100 participants, with recruitment evenly distributed across four centers (approximately 25 participants per center). This design ensures robust data collection while allowing for comparative analysis of the interventions.

Participants for this study will be recruited through invitation letters distributed via four associations located across Spain. Eligibility criteria for inclusion in the study are as follows: (a) a confirmed diagnosis of ID arising from neurodevelopmental disorders or autism spectrum disorders; (b) classification of moderate or mild ID (based on a combination of IQ (Intellectual Quotient) scores and adaptive behavior), as defined by the criteria of the Spanish National Health System; and (c) Independent ambulatory ability.

The legal representatives or caregivers of potential participants will be responsible for consulting with the individuals, regarding their willingness to participate in the study and providing written consent on their behalf. Additionally, all participants will have the opportunity to express their own consent or assent regarding their involvement [29].

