#### 2.4.4. Cost-Effectiveness of the Program

To assess the cost-effectiveness of the intervention [38], we will use a cost-effectiveness ratio (CER), which quantifies the relationship between the total cost of the intervention and the improvement in the primary outcomes. In addition, the CER of improvement in QoL and functionality will be determined using the following formula:$$CER=\frac{TC}{\Delta E}$$
where

TC = Total cost of the program (NW or Fit 5-Fitness Cards);ΔE = Change in average outcomes scores (post-intervention minus pre-intervention).

The incremental cost-effectiveness ratio (ICER) will be computed to compare the economic and functional impact of NW against the Fit 5-Fitness Cards program. The ICER will be determined using the following equation [39]:$$ICER=\frac{C1-C0}{E1-E0}$$
where

C1 = Total cost of the NW intervention;C0 = Total cost of the Fit 5-Fitness Cards program;E1 = Post-intervention outcome for the NW group (e.g., average QoL score);E0 = Post-intervention outcome for the Fit 5-Fitness Cards group.

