#### 2.4.5. Post-Intervention Average Weekly Physical Activity

Before the intervention begins, the participants and their parents will be asked to write the main physical activities (modality and duration) that they usually perform together in a typical week. Once the intervention ends (7 months after the start of the exercise program), a physical activity log will be given to the participants and their parents. They will be asked to register any type of physical activity (modality and duration) performed during a typical week of each month for the following six months.

Four NW poles will be given to the participants (two) and their parents (two) who complete the whole intervention. They will be encouraged to continue practicing NW by themselves for the next six months. Additionally, the registered offices that took part in the research will allow the use of the facilities in which the Fit 5-Fitness Cards and NW program took place at least two days per week, so that the participants and their parents could keep performing Fit 5-Fitness Cards and NW activities, also for the next six months.

Health-related PF, feasibility and QoL measurements will be carried out one week before the start of the training programs (To), once a week after the completion of the first stage (T1), one month later (T2), at the end of the second phase (T3), and six months later (T4). Record logs will be returned at T0 and T4. All the field-based tests and the questionnaire will be administered by the people in charge of the exercise intervention performed in each ID registered office.

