### 2.6. Statistical Analysis

Data will be reported as medians and interquartile ranges for non-normally distributed variables (checked with the Kolmogorov-Smirnoff test) or as means and standard deviations for normally distributed variables. Qualitative variables will be reported as n (%). The intra-cluster correlation coefficient and the cluster-specific effects will also be calculated. Inter-group quantitative variables will be compared, including the primary outcome, with an unpaired, two-tailed t test or the Mann–Whitney U test, as applicable. For inter-group dichotomous data comparison, the two-tailed chi-square tests will be used, with the Yates correction or Fisher’s exact test as appropriate. For repeated measures analysis, the two-way analysis of variance with the Bonferroni correction or the Friedman test, as appropriate, will be used. Comparison will be adjusted by cluster effect. Subgroup analysis of the primary outcome will include sex, age, BMI (normal, overweight and obese), level of physical activity (Inactive, Active), and level of ID (mild, moderate, severe). Multivariate regression models will adjust for confounders such as sex, age, BMI, physical activity, and ID level. Multicollinearity will be checked using the Variance Inflation Factor (VIF), with VIF > 5 indicating high collinearity [42]. Sensitivity analyses will assess robustness. Statistical significance will be set at a two-tailed *p*-value of less than 0.05. All analyses will be conducted using SPSS v24.0 software (IBM Corp., Armonk, NY, USA).

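### The repeated-measures ANOVA or Friedman test named in section 2.6 uses only participants with every entered visit, so partial records drop out of the within-person analysis

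*Protocol article*

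**What the plan says.** Section 2.6 gives one rule for longitudinal data: "For repeated measures analysis, the two-way analysis of variance with the Bonferroni correction or the Friedman test, as appropriate, will be used". It also says that "All analyses will be conducted using SPSS v24.0 software". It names no mixed model and does not say which visits enter the repeated-measures test.

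Section 2.4.5 schedules fitness, feasibility and quality-of-life measurements before the programmes (T0), after the first stage (T1), and then "one month later (T2), at the end of the second phase (T3), and six months later (T4". T0 and T1 therefore bracket the first programme, T2 and T3 bracket the second, and T4 closes the six-month follow-up.

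Section 2.2 arrives at 67 participants and adds: "To account for potential dropouts, the final sample size was set at 100 participants". It states no dropout rate.

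Between-group comparisons have their own rule in section 2.6: "Inter-group quantitative variables will be compared, including the primary outcome, with an unpaired, two-tailed t test or the Mann–Whitney U test, as applicable".

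**The concern.** The Friedman test needs a complete block for each person. The usual SPSS repeated-measures ANOVA deletes anyone with a missing value at any visit entered. A participant who completes the first programme, is measured at T0 and T1, and leaves during the washout would then contribute nothing to the within-person analysis, although the first-programme change was observed. If T4 is entered, a participant with all of T0 to T3 is also lost for missing one follow-up visit, at a time when everyone has been offered both programmes and no clean programme contrast remains.

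This matters because section 2.1 justifies the crossover by within-subject comparison, section 2.2 sizes the trial on a paired test, and the repeated-measures rule is the only test named in section 2.6 that is explicitly within-person. Discarding collected data lowers precision. If people who respond differently are more or less likely to leave, the within-programme change among complete cases also differs from the change among everyone measured.

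**Working it through.** **The plan's own figure.** The only figure on loss is the step from 67 to 100. It implies an allowance of 1 − 67/100 = 33%, and 67/(1 − 0.33) = 100. The rate is implied, not stated. (The 67 is not reproduced by a two-sided signed-rank calculation at d = 0.5, which gives about 35. That is a separate matter and does not bear on this point.)

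**Records kept, by visits entered.** The documents give no missed-visit rate, so a rate p is assumed. If a proportion p is lost at each visit after T0, the proportion with complete data through k later visits is (1 − p)^k.

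| Assumed p | T0–T1: (1 − p) | T0–T3: (1 − p)³ | T0–T4: (1 − p)⁴ |
|---|---|---|---|
| 5% | 95.0% | 0.95³ = 85.7% | 0.95⁴ = 81.5% |
| 10% | 90.0% | 0.90³ = 72.9% | 0.90⁴ = 65.6% |
| 15% | 85.0% | 0.85³ = 61.4% | 0.85⁴ = 52.2% |

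**Observed first-programme pairs discarded, per 100 participants at p = 10%.**
- If T0–T3 are entered: 90.0 − 72.9 = 17.1.
- If T0–T4 are entered: 90.0 − 65.6 = 24.4.
- Attributable to T4 alone: 72.9 − 65.6 = 7.3.

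Most of the discarding therefore remains even if T4 is left out.

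**At the implied allowance.** If 33% have withdrawn by T3 and 0%, 10% or 20% of the rest miss T4, a five-visit analysis keeps 100 × 0.67 × 1.0 = 67, 100 × 0.67 × 0.9 = 60, or 100 × 0.67 × 0.8 = 54 people.

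**Can it bias?** A simulation with assumed values shows the mechanism. The mean T1 − T0 change was set at 0.50. Withdrawal after T1 was made likelier for those with a smaller change (21% withdrew), and 15% missed T4 at random. Five-visit completers were 67% of the sample and their mean T1 − T0 change was 0.64, an excess of 0.64 − 0.50 = 0.14. In this set-up everyone's T1 value was observed before withdrawal, so the complete-case rule itself creates the gap. With the opposite relation between response and leaving, the sign would reverse. With none, there would be a loss of precision only.

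**The case against.** Several parts of the opposing case stand and limit the point.

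- **T4 may not be entered.** Section 2.4.5 is a measurement schedule, and section 2.5 calls the last six months a follow-up phase. A reader might infer a five-visit test, but the text does not say so, and an analysis of T0 to T3 fits equally well. The T4 loss is therefore conditional. The loss of those who leave after the first programme is not removed by this.
- **The trial's results do not all describe completers.** That is a tempting inference, but section 2.6 assigns inter-group comparison, including the primary outcome, to an unpaired t test or Mann–Whitney U. Either can use everyone measured at that visit.
- **An upward bias in the Nordic Walking effect is not shown.** Assuming that a third leave and gain 0.3 to 0.5 SD less gives 0.33 × 0.3 = 0.10 to 0.33 × 0.5 = 0.17 SD. That is the whole gap between completers and all participants under assumed values. A mixed model recovers only part of it, because people lost before T1 have no observed programme response. For Nordic Walking against Fit 5, the direction depends on differential loss, on which the documents are silent.
- **A missing-data rule, or a rule on following people who stop a programme, is not required here.** A condensed article may leave both to the full protocol or analysis plan. The article also says "Sensitivity analyses will assess robustness" without detail. The point rests on the methods that are named.
- **Section 2.4.4 adds nothing.** It defines the cost-effectiveness effect as "Change in average outcomes scores (post-intervention minus pre-intervention". A reader might suppose that the two averages cover different people, but the text does not say so. For a fixed set of people, the change in averages equals the average change.

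A two-way ANOVA can also be fitted in ways that tolerate gaps. The article names none of them, and the Friedman alternative has no such latitude.

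**Conclusion.** The point holds for the repeated-measures analysis. As named, its methods are complete-case on whatever visits are entered, in a trial that schedules five visits and expects dropout. Under an assumed 5% to 15% loss per visit, complete records fall to between 85.7% and 61.4% for T0–T3, or between 81.5% and 52.2% for T0–T4, while 95% to 85% have the first before-and-after pair. The loss of collected data follows from the method once any entered visit is missed. Bias in the within-programme change requires in addition that leaving is related to response, and neither its direction nor its size can be read from the documents. The percentages rest on a constant assumed loss rate and on the standard SPSS form of the ANOVA.

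**What to change.** In section 2.6, replace the ANOVA/Friedman rule with a linear mixed model (the MIXED procedure in the SPSS package already named) fitted to all observed visits. Include programme, period and sequence as fixed effects, and terms for centre and participant. Take programme effects from T0 to T3, and analyse T4 separately as follow-up. This settles which visits enter, and the centre term also serves the cluster adjustment that section 2.6 promises.

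The cost is a change of wording, with no new data collection. There are three modest downsides. The model relies on a missing-at-random assumption. It brings distributional assumptions where the Friedman test would have been used. Four centres give little information on the centre variance, so that component will be poorly estimated.

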## 2. Materials and Methods

### 2.1. Study Design

This is a pilot study employing a crossover, cluster-randomized design with repeated measures. This design allows for a within-subject comparison, reducing inter-individual variability and increasing statistical efficiency compared to parallel-group trials, where each subject receives only one treatment [27]. Participating centers will be randomized in a 1:1 ratio into two groups. Two sequential interventions (NW program and Fit 5-Fitness Cards) will be conducted, separated by a 4-week washout period to mitigate potential carryover effects [27]. Following the washout period, the interventions will be repeated in reverse order, adhering strictly to the established protocol. A comprehensive outline of the design and procedures is presented in Figure 1.

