### 2.3. Procedures

The registered sites will be randomly assigned to two groups using a random number table generated in Excel. The randomization process will be unrestricted, with no stratification or pairing of sites. To minimize selection bias, allocation concealment will be ensured by having an independent researcher generate the randomization sequence and store it in a secure file. Following the recruitment of the participating sites and the completion of the training period for monitors/caregivers, the randomization table will be unblinded, and the sites will be allocated to one of two groups. Preferably, the monitors/caregivers will be occupational therapists, physiotherapists, or social workers with specialized training in adapted exercise.

Group A will initially implement the NW program, followed by the Fit 5-Fitness Cards program. Conversely, Group B will undertake the programs in the reverse order. The random sequence will be generated by [name], while [name] will be responsible for informing the registered sites of the exercise sequence their members are required to follow.

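### The tests named for the programme comparison treat participants as independent in a four-centre cluster crossover, and the one-line cluster adjustment does not say how that is put right, so error rates and intervals can be wrong

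*Protocol article*

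**What the plan says.** Section 2.1 of the protocol article defines the trial: "This is a pilot study employing a crossover, cluster-randomized design with repeated measures". The centre is the unit of allocation: "Participating centers will be randomized in a 1:1 ratio into two groups". Section 2.2 plans four centres with about 25 participants each, 100 in all. Section 2.3 adds "The randomization process will be unrestricted, with no stratification or pairing of sites".

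Section 2.6 names the tests. Group comparisons of quantitative variables, the primary outcome among them, use an unpaired two-tailed t test or Mann–Whitney U. Dichotomous data use chi-square or Fisher's exact test. Repeated measures use two-way ANOVA or Friedman. Significance is two-tailed at 0.05. Two sentences deal with clustering: "The intra-cluster correlation coefficient and the cluster-specific effects will also be calculated" and "Comparison will be adjusted by cluster effect". The regression models list sex, age, BMI, physical activity and level of disability as examples of confounders. Neither centre nor period is among them.

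**The concern.** Centres are allocated but participants are analysed. The named tests, in their standard form, treat the roughly 100 participants as independent. The adjustment sentence does not say which comparison is adjusted or how, and what a centre term does depends on the comparison:

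- **Within-person comparison of the two programmes.** Each person is seen under both programmes in the same centre. A stable centre effect therefore drops out of the contrast, and a centre intercept in a model of raw scores changes nothing. What remains is variation in a centre from one period to the next. The document makes such variation plausible: the tests and questionnaire are "administered by the people in charge of the exercise intervention performed in each ID registered office", those staff are unblinded (section 2.4), and the two phases are separated by a one-month washout (section 2.5).
- **Group A versus Group B in one period.** Centre is nested in group. The centre effect does not cancel, and a fixed centre effect cannot be separated from the group contrast.

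At stake are the two-tailed 0.05 level and the width of the interval for the programme difference, in a paper that would tell readers clustering had been handled.

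**Working it through.** **Inputs from the protocol article.** Four centres, m = 25 per centre, two-tailed 0.05, d = 0.5 (sections 2.2 and 2.6). The calculation takes two centres per sequence, as the 1:1 ratio implies, although unrestricted randomisation does not guarantee it.

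**Assumptions, because the document gives no correlations.** Total variance 1. Within-period ICC 0.05. Ratio k of between-period to within-period ICC 0.5 or 0.8. Within-person correlation r 0.5 or 0.7. No true programme difference.

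- centre variance = ICC × k
- centre-by-period variance = ICC × (1 − k)
- residual variance = (1 − ICC) × (1 − r)

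**1. The nominal level first.** With only a stable centre effect (k = 1), the person-level crossover t test rejected in about 5% of simulated trials. Adding a large centre effect to one data set left the estimate (0.127) and its standard error (0.0743 on 98 df) unchanged. So the test is valid if there is no centre-by-period variation, and a centre intercept plays no part in it.

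**2. Within-person comparison with centre-by-period variation.** True variance divided by the variance the test assumes is

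V = 1 + m × (centre-by-period variance) / (residual variance).

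The approximate false-positive rate is 2 × [1 − Φ(1.96/√V)]. The last column comes from 20,000 simulated trials per row.

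| k | r | V | Approximation | Simulated |
|---|---|---|---|---|
| 0.8 | 0.5 | 1 + 25 × 0.010/0.475 = 1.53 | 11% | 11% |
| 0.8 | 0.7 | 1 + 25 × 0.010/0.285 = 1.88 | 15% | 15% |
| 0.5 | 0.5 | 1 + 25 × 0.025/0.475 = 2.32 | 20% | 19% |
| 0.5 | 0.7 | 1 + 25 × 0.025/0.285 = 3.19 | 27% | 26% |

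With the ICC varied from 0.01 to 0.10 over the same k and r, the range is about 6% to 39%.

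**3. Group A versus Group B in one period, unpaired t test.** Design effect = 1 + (25 − 1) × 0.05 = 2.2. False-positive rate = 2 × [1 − Φ(1.96/√2.2)] = 18.6%; simulation gave about 19%.

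**4. Unpaired t test of the programmes pooled over both periods.** This ignores the pairing. True over assumed variance is residual variance + m × (centre-by-period variance). In the order of the table it is 0.73, 0.54, 1.10 and 0.91. Simulated false-positive rates were about 2.5%, 0.8%, 6.5% and 4%: too low in three of the four settings and slightly too high in one.

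**5. Centre-level t test.** Four centre means of the within-person period difference, compared between sequences on 4 − 2 = 2 df, gave about 5% in every setting.

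**6. Power on 2 df.** The critical value is 4.30 instead of 1.98. For d = 0.5 in units of the within-person difference and N = 100, the noncentrality is 0.5 × √(100/deff), with deff = 1 + 24 × (ICC of the differences).

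| ICC of differences | deff | Noncentrality | Power |
|---|---|---|---|
| 0 | 1.00 | 5.00 | 0.72 |
| 0.01 | 1.24 | 4.49 | 0.64 |
| 0.05 | 2.20 | 3.37 | 0.45 |
| 0.10 | 3.40 | 2.71 | 0.34 |

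**The case against.** The strongest reply is that section 2.6 does promise an adjustment, while the rates of 11% to 26% describe an analysis without an effective one. A random centre term fitted to the within-person differences captures exactly the centre-by-period variation, and a single correlation of those differences would represent it. Simulated with Satterthwaite degrees of freedom, that analysis had error rates of 3.6%, 5.4% and 7.4% in three of the assumed settings. The two-way ANOVA can also take a centre factor, and cluster-adjusted forms of the t, chi-square and rank tests exist. Model details are usually left to an analysis plan, which is not shown.

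Much of this stands. A reader might infer that p-values will always be too small, that no centre term could help, or that the named tests can never be adjusted. The document supports none of these: the size depends on correlations it does not give, and the pooled unpaired test usually errs the other way. Nor do the policy recommendations in the Discussion rest on the between-programme p-value; they concern an expected improvement with Nordic Walking.

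What does not stand is that the matter is merely left open. Section 2.6 names an unpaired test for the primary outcome, which does not use the within-subject comparison that section 2.1 gives as the reason for a crossover. With only four centres the form of adjustment also matters. At a single visit with an assumed ICC of 0.05, a design effect with an estimated ICC gave about 11% and robust standard errors with a normal reference about 30%. The text does not say that either would be used, but it excludes neither.

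**Conclusion.** The point holds in a conditional form. The article fixes tests that do not fit a four-centre cluster crossover and adds an adjustment too loosely worded to repair them. Error rates and intervals can therefore be wrong, in a direction that depends on the comparison made. Under the assumptions above (ICC 0.05), and without effective adjustment, the false-positive rate is about 11% to 26% within person, about 19% in a single-period unpaired t test, and about 1% to 7%, usually below 5%, in an unpaired test pooled over periods. If centre-by-period variation is absent, the within-person test keeps its 5%. A single reported ICC of the raw scores would not show which case applies, because it does not separate within-period from between-period correlation. The finding concerns the validity of the planned comparison, not the sample-size calculation.

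**What to change.** In section 2.6, replace the adjustment sentence and the unpaired test of the primary outcome with one crossover analysis. For each centre, take the mean within-person difference between periods. Compare these means between the two sequences by a t test with a 95% confidence interval on 2 df.

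An alternative that only approximates this is a linear mixed model with programme, period and sequence as fixed effects; centre, centre-by-period and participant as random effects; and small-sample degrees of freedom. It is not equivalent. In simulations of the corresponding model for the within-person differences, the centre-by-period variance was estimated as zero in 15% to 60% of trials, and the test then falls back to about 98 df.

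Report the within-period and between-period correlations rather than one coefficient. As this is a pilot, present the programme difference as an estimate with its interval, not as a confirmatory test.

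No new data are needed. The cost is wider intervals and lower power: at d = 0.5 and N = 100, 0.72 with no centre variation in the differences and 0.45 if their ICC is 0.05. That follows from having four centres and should be stated openly.

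### The BMI subgroup levels have no place for underweight participants, and cutting BMI and activity into classes lowers the chance of seeing whether the effect varies with them

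*Protocol article*

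**What the plan says.** - **Subgroup levels (2.6, Statistical Analysis).** "Subgroup analysis of the primary outcome will include sex, age, BMI" and further factors, with the levels "BMI (normal, overweight and obese), level of physical activity (Inactive, Active". Sex, age and level of ID are the other factors, and age is given no classes. No BMI boundaries, activity threshold or subgroup test are stated.
- **Regression (2.6).** "Multivariate regression models will adjust for confounders such as sex, age, BMI, physical activity, and ID level". The form of BMI and activity in these models, continuous or classed, is not stated.
- **Eligibility (2.2, Participants).** There are three criteria: "a) a confirmed diagnosis of ID arising from neurodevelopmental disorders or autism spectrum disorders"; a "classification of moderate or mild ID"; and "c) Independent ambulatory ability". None concerns weight, BMI or activity.
- **Baseline activity (2.4.5).** Participants and parents are to "write the main physical activities (modality and duration) that they usually perform together in a typical week".
- **Sample size (2.2).** 67 participants are required, and the target is raised to 100 for dropout. No power is given for any subgroup analysis.

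**The concern.** Two separate things are wrong with the stated levels.

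1. **The BMI list is incomplete.** The entry criteria admit underweight people, but the list starts at normal weight. Read as written, these participants have no place in the BMI subgroup analysis.
2. **Graded measures are cut.** BMI is a number, and the baseline record asks for durations. A class treats everyone in it as alike. If the programme effect changes gradually with BMI or activity, part of that signal is lost.

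At stake is one secondary question: for whom NW works better or worse than Fit 5. With 67 to 100 people the power to answer it is limited already. The objection is to the levels that the plan does state, not to the lack of a stated interaction test or multiplicity rule.

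**Working it through.** **The plan's own figure.** There is none to reproduce on this point. From the article I use only the two sample sizes (67 and 100) and the two-sided 0.05 level.

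**Assumptions that are not in the article.** The within-person NW minus Fit 5 difference is linear in BMI with correlation r = 0.30. Participants are independent. BMI is normal with mean 27 and SD 5, or mean 29 and SD 6. Class boundaries are 18.5, 25 and 30.

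**Step 1: share with no BMI level.** Φ((18.5 − 27)/5) = Φ(−1.70) = 0.045, and Φ((18.5 − 29)/6) = Φ(−1.75) = 0.040. That is about 4%, or roughly 3 of 67 and 4 of 100.

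**Step 2: information kept after cutting.** For a two-way split with upper share p and c = Φ⁻¹(1 − p), the share of a linear modifier's information that is kept is φ(c)²/[p(1 − p)]:
- 50/50 split: 0.399²/0.25 = 0.64
- 30/70 split: 0.58
- 20/80 split: 0.49

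For three classes it is Σ pₖmₖ², where pₖ is the class share and mₖ the mean standardised BMI in the class. With boundaries at 25 and 30 this is 0.80 for N(27, 5) and 0.78 for N(29, 6). Three BMI classes therefore keep most of the information. Much of the further loss comes from spending two degrees of freedom on an unordered test.

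**Step 3: power by formula.** The noncentrality is λ = n·ρ²/(1 − ρ²), with ρ² = 0.09 times the share kept. At n = 67:
- Continuous: 67 × 0.09/0.91 = 6.63, power 0.72.
- Median split: ρ² = 0.0573, λ = 4.07, power 0.51.
- Three classes, everyone kept, 2 df: λ = 5.05 to 5.21, power 0.49 to 0.50.

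**Step 4: power by simulation** (4,000 runs per setting, BMI drawn at random; ranges are over the two BMI distributions and repeated runs).

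| Analysis, r = 0.30 | n = 67 | n = 100 |
|---|---|---|
| Continuous BMI | 0.69–0.70 | 0.86–0.87 |
| Three classes, trend test | 0.59–0.60 | 0.77–0.78 |
| Three classes, everyone kept, 2 df | 0.48–0.49 | 0.67–0.69 |
| Three classes, underweight dropped, 2 df | 0.39–0.41 | 0.56–0.59 |
| Median split | 0.49–0.50 | 0.67–0.68 |

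At n = 67 the loss is about 10 points for ordered classes, 20 for a median split, 21 for unordered classes and 30 when the underweight tail is also dropped.

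**Step 5: how far the loss depends on the assumptions.** I let the continuous analysis have 30% to 95% power, and took two-way splits from 50/50 to 10/90 and three classes on 2 df with everyone kept. The loss then runs from 9.3 to 46.2 points. It is largest for very uneven splits, which an undefined activity threshold could produce. If the true effect is a step exactly at the activity cut, the split does better: 0.81 against 0.63 for the continuous analysis.

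**The case against.** The strongest reply is that little of the power loss belongs to the plan. Section 2.6 names no subgroup test and gives no BMI boundaries. The larger losses need an unordered 2-df test and deletion of the underweight tail, and the plan commits to neither. An ordered test on the same classes costs only about 8 to 11 points. The figures describe a within-person contrast with independent people, whereas 2.6 plans group comparisons adjusted for cluster. The article also condenses a pilot protocol, and placing a few underweight people is a detail that a fuller document might settle.

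All of this limits the size of the point, so the figures can only be illustrative. It does not remove the point: the article lists BMI levels that do not cover its own eligible population, and it chooses classes where graded values exist.

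The reply is also right about several stronger readings that a reader might infer:
- **Both factors leave people out.** Only the BMI list does. Inactive and Active together cover everyone; the weakness there is the cut and its missing threshold.
- **Underweight people are lost to the whole trial analysis.** Nothing shows this. The regression may already use continuous BMI.
- **Cutting discards most of the information.** This is false for three BMI classes, which keep roughly 76 to 80% over the class shares tried, and for a median split, which keeps 64%.
- **The loss is a fixed 20 to 30 points.** It is not; it depends on unstated assumptions and can reverse.

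Finally, analysing continuous moderators is itself an interaction analysis, and should be described as one.

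**Conclusion.** The point holds as a minor, inexpensive improvement.

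The gap in the BMI levels follows from the text alone: underweight participants are eligible and have no level in the BMI subgroup analysis. How many there would be is unknown; about 4% is an assumption.

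The cost of cutting is conditional. With a linear modifier of r = 0.30 and independent participants, power for BMI drops from about 0.70 to between 0.40 and 0.60 at n = 67, and from about 0.86 to between 0.58 and 0.77 at n = 100, depending on the test and on what is done with underweight participants. Over wider assumptions, splits and unordered classes lose about 9 to 46 points. Clustering in four centers is ignored and would lower all absolute values. The simulation was run for BMI; carrying it over to activity assumes a similarly well-behaved measure.

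**What to change.** In 2.6, state three things:

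1. BMI is analysed as a continuous moderator of the NW versus Fit 5 effect on the primary outcome, with a check for non-linearity such as a quadratic term.
2. Baseline activity is treated the same way where the baseline record gives usable weekly minutes. Otherwise, define the threshold between Inactive and Active.
3. Classes are for display only, and the display gives underweight participants a level of their own or says which level they join.

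No change is needed for age, which the plan does not cut. For the regression it is enough to state the form in which BMI and activity enter.

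The cost is a few sentences and no new data. The downside is that a linear form is assumed and the result is read as a slope rather than as familiar classes. The baseline activity record is also a limited source: it is self-reported and covers only what participants and parents do together, so derived minutes will understate total activity. An Inactive/Active split built from the same record would share that weakness.
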